#### Allocation

Schools were randomised to intervention or control using a computer-generated simple-randomisation sequence by an independent statistician who was masked to school identity. All schools and children were recruited prior to randomisation. All baseline measurements were conducted prior to randomisaton.

#### Blinding

Researchers will be masked to intervention group at post-test. To maintain masking of researchers, observers and interviewers will not be informed of the study design, and will be employed during the measurement phases of the study only. Intervention and control schools will be provided with the same educational materials. Teachers will be asked not to reveal their school's intervention status to data collectors. Where research assistants collect data at more than one timepoint (eg, baseline and post-test), they will be rotated across schools and classrooms, so they do not observe the same classroom from one timepoint to the next, and hence, are not able to detect changes to teacher competencies.

#### Data management

Data will be double-entered into OpenClinca V.3.1 by two independent data entry personnel. The OpenClinica database includes a series of logical data checks, with errors generating queries. The status of all data queries will be maintained in an automated query system which forms part of the OpenClinica installation. Sign-off (electronic signature) will be required at each review resolution and at the finalisation of the data series for each participant. Trial-related electronic information will be stored on a dedicated data server with restricted and documented human access. Automated daily backups are performed to a distinct data server, and weekly offsite backups to ensure a geographically separated data copy. Hard copy questionnaires will be scanned, with scanned copies stored in a secure document repository (AlFresco software) on the same data server and subject to the same backup regime. Hard copy questionnaires will be stored in a secure physical location with restricted human access, and with any participant identifiers kept separately from trial data.

#### Statistical methods

The effect of intervention will be examined on an intention-to-treat basis, using multilevel multiple regression models for continuous outcomes and random effects logistical regression models for binary outcomes (and random effect for count outcomes such as Poisson or Negative Binomial if required), to take into account the hierarchical structure of the study. Tester/observer and intervention status (and child age and sex for child-level data) will be entered as fixed effects, and school (and classroom) entered as random effects.

Few studies have reported on mediators of intervention effectiveness in school-based preventative trials. We will explore whether change in teacher depression, self-efficacy and burn-out mediate the effect of intervention on teachers’ use of violence and levels of classroom aggression using standard techniques for multilevel mediation analyses. We will also examine whether teachers’ use of violence and the quality of the classroom environment mediate the effect of intervention on child mental health, self-regulation and attendance. Potential moderators of intervention effectiveness will also be investigated. We will examine whether teachers who use high levels of violence against children at baseline, and whether classrooms characterised by high levels of child aggression at baseline, benefit most from the intervention. We will also examine whether the child's sex moderates the effect of intervention on child mental health, social skills, self-regulation and school attendance.

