### Outcome measures

All measures are collected at baseline (in the summer term of 2015) and will be repeated at post-test (summer term of 2016). All classroom and teacher-level outcomes will also be collected at 1-year follow-up (summer term of 2017). Classroom and teacher-level outcomes will be collected in the control schools only in the summer term of 2018.

All data are collected by research assistants using pencil and paper methods. Data collectors will be trained over a minimum of a 4-week period before each round of measurements. Inter-rater reliabilities will be assessed for all measures, and values of over r>0.8 will be required. Training will continue until this standard is attained. Ongoing inter-rater reliabilities will be conducted on a minimum of 5% of all measurements. Observers and testers will be rotated across classrooms and schools to ensure any variance among data collectors is not systematic. Data will be monitored weekly for such systematic variation and to ensure inter-rater reliabilities >0.8 are maintained. All questionnaire and test data will be checked by the trial manager on a daily basis for missing or erroneous data, and data will be checked weekly by a content expert to monitor compliance with the data collection protocols.

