### Sample size

The trial has two primary outcomes: level of class-wide aggression and violence against children. Using Tukey's method of correction for multiple testing,^33^ we require a significance level of 0.036 in each individual test to keep a Family-Wise Error Rate of 0.05.

Level of class-wide aggression. In a parallel group design, 72 classes in each group are sufficient to detect an ES of 0.5 SD, with 81% power at 0.05 level of significance. With a cluster size of three (3 classrooms/school), and assuming an intraclass correlation (ICC) of 0.25, the design effect is 1.5 (design effect=1+(cluster size–1)×ICC)) giving a required sample size of 108 classrooms per group, which yields 36 schools per group. We will recruit 38 schools (114 classrooms) per group (76 schools in total) to allow for 9% teacher loss.

Violence against children by teachers. In a parallel group design, 90 classes in each group are sufficient to detect a reduction from 60% to 35% with 87% power at 0.05 level of significance. With a cluster size of three (3 classrooms/school) and an ICC of 0.1 (based on data from our efficacy trial), the design effect is 1.2, giving a required sample size of 108 classrooms per group, which yields 36 schools in each group. As mentioned above, we will recruit two additional schools per group.

The analyses of the secondary outcomes is considered exploratory, and the significance level of the tests will not be adjusted for comparisons of multiple outcome.

Classroom and teacher-level measures. Similar to the primary outcome of level of classwide aggressions, we have 85% power at a 0.05 level of significance to detect a difference of 0.5 SD on the quality of the classroom environment and on teacher depression, self-efficacy and burn-out.

Child-level measures. In a parallel group design, 252 children in each group are required to detect a difference of 0.25 SD with 80% power at 0.05 level of significance. With 11 children per school, and an estimated intracluster correlation coefficient of 0.05, the design effect is 1.50 giving a required sample size of 378 children and 36 schools in each group. Our proposed sample includes 38 schools/group. We recruited children from the 4-year-old class: in classes with 12 or fewer children, all children were recruited; where there were more than 12 children, a random sample of 12 children were selected. The maximum sample size was 456 children/group.

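### The stated effect model omits the baseline value of the outcome, although every measure is taken before randomisation; precision is forgone and chance imbalance stays in the realised estimate

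*Protocol article*

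**What the plan says.** The Statistical methods section describes multilevel regression for continuous outcomes and random-effects logistic regression for binary ones, with count models if required. It then names the terms: "Tester/observer and intervention status (and child age and sex for child-level data) will be entered as fixed effects", with "school (and classroom) entered as random effects". For the main effect analysis it mentions no baseline outcome, change score or repeated-measures term.

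Baseline values exist for every outcome. Under Outcome measures: "All measures are collected at baseline (in the summer term of 2015) and will be repeated at post-test (summer term of 2016". Under Allocation: "All baseline measurements were conducted prior to randomisaton". The same section says "Schools were randomised to intervention or control using a computer-generated simple-randomisation sequence", and mentions no stratification or matching.

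Baseline levels of the primary outcomes enter the plan only as possible moderators, for instance "We will examine whether teachers who use high levels of violence against children at baseline", with a parallel question about classrooms that are highly aggressive at baseline. Change is mentioned only for the teacher-level mediators (depression, self-efficacy, burn-out).

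**The concern.** A baseline measurement of the outcome, taken before allocation, is usually the most useful covariate available. Here it has been collected for every measure, and the authors intend to use it for moderation, yet the model that estimates the intervention effect leaves it out. The list is detailed enough to include observer, age and sex, so the omission is a feature of the model as published.

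Two things are at stake. First, any variance in the post-test score that baseline could explain stays in the residual, and the interval is wider than it need be. Second, simple randomisation of 76 schools does nothing to balance baseline levels, so adjustment in the analysis is the remaining place to remove a chance difference from the one allocation that was realised.

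**Working it through.** **Inputs from the Sample size section.** Aggression: 72 classes per arm before the design effect, difference 0.5 SD, stated power 81%, intraclass correlation 0.25, three classrooms per school. Per-test level: "we require a significance level of 0.036 in each individual test to keep a Family-Wise Error Rate of 0.05". Child outcomes: 252 children per arm before the design effect, 0.25 SD, 80% power at 0.05. Tests are taken as two-sided.

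**Input not in the document.** The baseline to post-test correlation r. It is shown over a range, and taken to be the same at school and class level.

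**Step 1: reproduce the stated figure.** The design effect is 1 + (3 − 1) × 0.25 = 1.5, and 72 × 1.5 = 108 classes, or 36 schools per arm, as stated. With no baseline term the noncentrality is 0.5 × √(72/2) = 3.00. The noncentral t power is 81.1% at level 0.036 and 84.6% at 0.05. The stated 81% therefore corresponds to the 0.036 level and takes no credit for baseline.

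**Step 2: add baseline.** Adjustment multiplies the residual variance by (1 − r²), equivalent to 72/(1 − r²) effective classes per arm. Interval width is multiplied by √(1 − r²).

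| Assumed r | 1 − r² | Effective classes per arm | Power at 0.036 | Interval narrower by |
|---|---|---|---|---|
| 0 | 1.00 | 72.0 | 81.1% | 0% |
| 0.1 | 0.99 | 72.7 | 81.5% | 0.5% |
| 0.2 | 0.96 | 75.0 | 82.7% | 2% |
| 0.3 | 0.91 | 79.1 | 84.7% | 5% |
| 0.5 | 0.75 | 96.0 | 91.1% | 13% |
| 0.6 | 0.64 | 112.5 | 94.9% | 20% |

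For the child outcomes the same factor (normal approximation, level 0.05) moves power from 80.1% at r = 0 to 83.7% at r = 0.3 and 90.0% at r = 0.5.

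**Step 3: chance imbalance.** If the same intraclass correlation applies at baseline, the standard error of the baseline difference between arms is √(2/72) = 0.167 SD. The probability that it exceeds 0.2 SD in either direction is 2 × [1 − Φ(0.2/0.167)] = 2 × [1 − Φ(1.2)] = 23%. The unadjusted estimate is expected to carry r times the imbalance. For a 0.2 SD imbalance that is 0.06 SD at r = 0.3 and 0.10 SD at r = 0.5; the latter is one-fifth of the 0.5 SD target.

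**Violence outcome.** No figure is calculated. In a logistic model, adding baseline changes the odds ratio being estimated to one conditional on baseline, so the (1 − r²) factor is only a guide.

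**The case against.** The strongest reply is that this is one sentence in a journal article. It does not say that only these terms will be used, and an analysis plan that is not shown may add baseline. That is fair as far as it goes: a reader might infer a firm commitment to a comparison of post-test scores alone, and the text does not go so far as to exclude baseline. But the article does more than stay silent. It lists the covariates, and a later plan that added baseline would change the published model. The point is about the list as it stands.

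A reader might also infer that the trial is underpowered or its estimate biased. The documents do not support either. The 81% is reproduced with no baseline term, the unadjusted estimator is unbiased over repeated randomisations, the Type I error is unaffected, and the ordinary standard error already allows for chance imbalance.

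Nor can one say that a material imbalance is likely: the chance of exceeding 0.2 SD is 23%, and of exceeding 0.3 SD it is 7%.

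Finally, the gain may be small. Class ratings are made in the summer terms of two different academic years, so the pupils and possibly the teacher may differ. Under Blinding, observers are rotated so as not to see the same classroom twice. These features could make r low, and at r = 0.1 the gain is negligible. This objection stands as to size. It does not favour leaving baseline out, since an uninformative baseline costs about one degree of freedom.

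**Conclusion.** The point holds as a recommendation on efficiency. The published fixed-effect list leaves out a covariate that is already collected, is valid because it precedes allocation, and is nearly free to use. The consequence is forgone precision, together with any chance baseline difference remaining in the realised estimate; it is not a failure to reach the planned power and not a bias.

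For aggression the forgone power runs from under half a percentage point at r = 0.1 to about 14 points at r = 0.6. That range rests on assumed correlations, a common correlation at school and class level, and the protocol's own intraclass correlation and effect size. The gain for the binary violence outcome is not quantified. The change should be made, but the trial's primary conclusions do not depend on it.

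**What to change.** State, before any post-test data are seen, that each primary and secondary effect model includes the baseline value of the same outcome as a fixed effect: baseline class rating for classroom outcomes, the teacher's baseline value for teacher outcomes, and the child's own baseline score for child outcomes. The Trial status section reports the intervention as still underway, so at the time of the article this could be fixed in advance.

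Add a rule that keeps classes or teachers without a baseline in the analysis, for example the school baseline mean plus a missing-baseline indicator. For the logistic violence model, state that the reported odds ratio is conditional on baseline.

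The cost is one covariate per model, plus the indicator where baseline is missing. No new data are needed and the sample size does not change.

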#### Economic analysis

The goal of the economic analysis is twofold. First, we will assess the efficiency of classroom instruction (using observational data of the quality of the classroom environment and the level of childhood aggression). As a short-term indicator of the effectiveness, we will compare the costs of training with time saved in instruction attributed to reduced behavioural disturbances. This can be coupled with the data on benefits to child attendance (proportional to the total days so that a 5% increase of attendance is worth 5% of what a year of schooling is worth) to assess changes in classroom efficiency. We will link the observed changes in attendance and child self-regulation skills with data from other studies on preschool instruction, to provide a plausible range of expected long-term economic returns. By assessing the degree to which the changes in teacher behaviour are present a year after the interventions we will be able to assess whether the initial training costs need to be augmented with refresher training.

## Ethics and dissemination

School principals were visited by a senior member of the research team and were informed of the study and invited to participate. Once the principal had agreed, the teachers were approached individually by the same personnel, and informed consent was sought. Consent forms were sent home to parents of children selected to participate in the evaluation, and returned to the school.

Ethical consent for the study was given by the School of Psychology Ethics and Research Committee, Bangor University, on 29 October 2014 (ref: 2014-14167), and by the University of the West Indies Ethics Committee on 14/15 February 2015 (ref: ECP 50, 14/15).

The results of the study will be released to the participating schools and teachers, the Ministry of Education, the Early Childhood Commission, and teacher training institutions in Jamaica, and will be submitted to peer-reviewed journals regardless of the magnitude or direction of the effects.

## Discussion

There is significant evidence that early childhood education interventions can promote young children's development in LMIC,^34^ and many countries are investing in preschool provision; however, provision of high-quality preschool remains a challenge. Early childhood is a particularly sensitive period, as experiences in early childhood have long-term effects on brain function, cognition and psychosocial functioning. A safe (free from physical and psychological harm), secure (consistent and predictable), and nurturing (sensitive and responsive) early childhood caregiving environment promotes child physical and mental health over the long term.^35^ There is limited evidence of the effectiveness of interventions aimed at improving the quality of preschools in LMIC, although several small-scale studies have shown promising results to teacher practices and children's mental health.^36^ Through our previous work in Jamaica, we have shown that training teachers in evidence-based behaviour management strategies can reduce violence against children by teachers and reduce conduct problems and increase social skills in antisocial young children.^12^ Through this study, we will test whether a simplified and lower cost intervention, implemented on a larger scale will lead to meaningful benefits to teachers and children. If this intervention were effective at improving the caregiving environment of young children in school this would have significant implications for the prevention of child mental health problems in LMIC where services are often limited. As the intervention is integrated into the school system and involves training existing staff to improve their performance (rather than to undertake new duties), it represents an appropriate strategy for large-scale implementation.

### Trial status

The study began in January 2015. Baseline data collection was conducted from May to June 2015. Intervention began in September and is currently underway.
